### Quantitative assessment and analytic plan

The primary outcome measure for the study is change in sexual violence. Other secondary outcomes include physical/emotional abuse, healthy relationships, and self-esteem, for example. Hypothesized directions of changes, primary and secondary outcomes, and measures are found in Table 3. Scales were tested through cognitive interviewing techniques prior to the baseline and adapted as needed in both countries. All study tools were translated into local languages and back-translated into English.

**Table 3 Tab3:** Primary and secondary outcomes and hypothesized direction of change

	Hypothesized direction of change	Source of measure
Girl Primary Outcomes		
Past-Year Sexual Violence	Decrease	Adapted from CDC Violence Against Children Survey [39]
Girl Secondary Outcomes (Slight variations by country)		
Past-Year Positive Interpersonal Relationships	Increase	Adapted from CDC Violence Against Children Survey [39] & Sisters of Success Liberia survey [40]
Past-Year Early Marriage	Decrease	Adapted from CDC Violence Against Children Survey [39]
Past-Year Physical Violence & Emotional and Verbal Abuse	Decrease	Adapted from IPSCAN Child Abuse Screening Tools [41]
Self-Esteem	Increase	Rosenberg Self-Esteem Scale [42]
Gender Equitable Norms	Increase	Gender Relationship Scale [43]
Hope and Future Orientation	Increase	Children’s Hope Scale [44]
Accepting Attitudes towards domestic violence	Decrease	Demographic and Health Surveys (DHS) Domestic Violence Module [45]
Caregiver Outcomes (DRC Only)		
Parental Acceptance	Increase	Parental Acceptance-Rejection Questionnaire (Parent Short Form) [46]
Accepting Attitudes of Negative Discipline	Decrease	Adapted from Child Protection Knowledge, Attitudes, and Practices (KAP) in Liberia Survey [47]
Gender Equitable Norms	Increase	Gender Norms and Attitudes Scale [43]

In DRC, Audio Computer Administered Self Interviews (ACASI) software was used for sensitive violence questions and Computer-Administered Personal Interviews (CAPI) was used for non-sensitive questions for girls and for the full caregiver survey. Only the older groups of girls (aged 13–14) were asked violence and sexual health modules given ethical concerns.

In Ethiopia, ACASI was used for the entire survey due to challenges of hiring female enumerators who can both speak the local non-written languages selected for the study (Engsena Quickly, Funj/Berta, Maban, or Regarig) and read and write in Amharic, Arabic or English. ACASI was selected as a data collection method as it has been shown to increase reporting of sensitive behaviors [31] in addition to its ability to overcome the language and literacy challenges found among refugee camps in Western Ethiopia. Colors and images for response options were piloted and varied by country in the final ACASI programming.

Descriptive statistics and tests of variables of interest, including chi-square tests and t-tests, will be constructed. Generalized linear mixed models, also known as hierarchal/multilevel mixed models, will be used to assess whether girls in the intervention arm report changes in outcomes of interest compared to girls in the intervention arm, accounting for multiple levels of clustering in the data (time, family, group, village/refugee camp zone). Intention-to-treat analyses and per protocol analyses, based on attendance records, will be generated.

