### Randomization, sample size, and power analysis

Based on the assumptions of 80 % power to detect a Cohen’s effect size of d = 0.3 between treatment versus wait-list groups (α < 0.05 statistical significance level, a design effect of 2.0), a sample size of 704 girls is required in each country. After accounting for an expected attrition rate of 25 % in DRC, the final sample size required at least 880 girls and a total of 886 girls were surveyed at baseline. Primary caregivers of selected girls in DRC were also asked to participate in the study (n = 777 surveyed at baseline). In Ethiopia, given movement concerns within the refugee camps and higher likelihood of loss to follow-up and potential refusals at baseline, the attrition rate was inflated and a total of 919 girls were surveyed at baseline.

Groups are comprised of 20–25 girls each, based on geographic proximity or language. Groups of girls were divided into younger groups and older groups, given age-tailored content of programming. In DRC, 35 girl groups across 14 villages in South Kivu were divided into two age strata: 10–12 years of age and 13–14 years of age. In Ethiopia, 47 groups across three refugee camps were divided into age strata; group formation also accounted for school scheduling in the camps. Groups were first stratified by age level (13–14 years and 15–19 years) and then randomized to either the intervention or wait-list arm following the baseline survey. If sisters or girls who identified the same caregiver or reside in the same house were participating in the program, girls were assigned to the same group if they were in the same age category. If they were in separate age groups, the groups were paired together and randomized to the same study arm. Randomization was completed using the statistical software R version 3.2.1.

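### The primary outcome is worded as change in sexual violence, which is less precise than a baseline-adjusted endline comparison, and the 80% power is not expressed on that outcome

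*Protocol article*

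**What the plan says.** Under Quantitative assessment and analytic plan, the protocol article states: "The primary outcome measure for the study is change in sexual violence". Table 3 in the same section lists the one primary outcome for girls as "Past-Year Sexual Violence", with a decrease hypothesised. It does not say whether this is yes/no, a count or a score. The last paragraph of the section plans generalized linear mixed models for changes in outcomes between arms, with time, family, group and village or camp zone as levels of clustering. It does not say how the baseline response enters the model.

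Under Randomization, sample size, and power analysis, the calculation assumes "80 % power to detect a Cohen’s effect size of d = 0.3 between treatment versus wait-list groups" with "α < 0.05 statistical significance level, a design effect of 2.0", and concludes that "a sample size of 704 girls is required in each country". No outcome, prevalence, percentage-point difference or baseline-endline correlation is attached to d = 0.3. The same section says that groups were randomised after the baseline survey.

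**The concern.** Two published statements do not fit together well. The power figure is a generic standardised difference, while the primary outcome is change in a particular violence measure. A reader cannot tell what reduction in sexual violence the trials have 80% power to detect.

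The word change also matters for the estimate. Each girl's baseline response was collected before randomisation, so it can be used as a covariate. Subtracting it, or estimating an unconstrained arm-by-time contrast, adds the noise of the baseline measurement to the comparison. Adjusting for it removes only the part of the endline variance that baseline predicts. When baseline and endline are weakly correlated, the difference in precision is large.

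**Working it through.** **Inputs.** From the article: d = 0.3, power 80%, alpha 0.05, design effect 2.0, 704 girls per country. Assumed, because not stated: two-sided test, 1:1 allocation, baseline-endline correlation r, prevalence, and a yes/no scale for step 3.

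**1. Reproducing 704.** The two-sided two-sample t-test for d = 0.3 at 80% power needs 175.4 per arm, rounded up to 176. Two arms give 352, and 352 × 2.0 = 704, an exact match. (The normal approximation gives 175 per arm and 700.) The formula has no term for prevalence or for a repeated measurement.

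**2. Change versus baseline adjustment.** The effective number per arm is 704 / (2 × 2.0) = 176. On a linear scale, with d in endline SD units and the same SD at both times, the variance relative to a plain endline comparison is:

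- change: 2(1 − r)
- baseline-adjusted: 1 − r²

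The ratio is 2(1 − r)/(1 − r²) = 2/(1 + r), which exceeds 1 for every r below 1. With v as the variance factor, power = Φ(0.3 × √(176/2) / √v − 1.96) = Φ(2.814/√v − 1.96).

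| r | v, change | Power, change | v, adjusted | Power, adjusted | Ratio 2/(1 + r) |
|---|---|---|---|---|---|
| 0.2 | 1.60 | 60% | 0.96 | 82% | 1.67 |
| 0.3 | 1.40 | 66% | 0.91 | 84% | 1.54 |
| 0.5 | 1.00 | 80% | 0.75 | 90% | 1.33 |
| 0.7 | 0.60 | 95% | 0.51 | 98% | 1.18 |

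In girls, at r = 0.3, matching the planned power takes 704 × 1.40 = 986 with change and 704 × 0.91 = 641 with adjustment. Change meets the stated 80% at r = 0.5 and exceeds it above that, but adjustment is the more precise of the two in every row.

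**3. What 0.3 means if the outcome is yes/no.** On the arcsine scale, p₂ = sin²((2·arcsin√p₁ − 0.3)/2).

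| Control prevalence (assumed) | Intervention prevalence | Relative reduction |
|---|---|---|
| 10% | 2.9% | 71% |
| 20% | 9.5% | 52% |
| 30% | 17.4% | 42% |
| 40% | 26.0% | 35% |

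**4. Which girls these figures describe.** Steps 2 and 3 use 704 girls. In DRC only girls aged 13–14 were asked the violence questions (Quantitative assessment and analytic plan), and their number is not given. The figures therefore do not carry over to the DRC primary analysis.

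**The case against.** The strongest reply is that the article fixes no change-score analysis. It plans mixed models with time as a level, and such a model with a common baseline mean would avoid the loss. How baseline is handled may be settled in a full protocol or SAP that is not shown. This stands as far as it goes: a reader might infer that the plan prescribes change scores or an unconstrained arm-by-time contrast, and the article does not say so. What remains is that the article names change as the primary outcome and describes models of changes, so its stated target is the less efficient one.

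A reader might also infer that the trials have less than 80% power because change is analysed. The document does not support that. Cohen's d is unit-free. If 0.3 was standardised by the SD of change, 704 gives the stated power for change. If it is in endline SD units, the shortfall appears only for r below 0.5. That d refers to a single time point is an inference from the formula.

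Nor does the article say that the outcome is a prevalence. Yes/no is a plausible reading of a past-year experience, but the scale is not given. Finally, the variance factors belong to a linear model, and the table holds the design effect at 2.0 for both analyses. For a binary outcome in a generalized mixed model the figures are only approximate.

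The Discussion already warns that changes may be hard to see within the limited follow-up. That is a fair caution, but it does not say what the 80% refers to.

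**Conclusion.** The point holds in a conditional form. The stated 80% is a generic two-sample figure that cannot be read as power for past-year sexual violence. If the primary estimate is an arm difference in change, it has 2/(1 + r) times the variance of a baseline-adjusted estimate: 1.67 times at r = 0.2, falling to 1.18 times at r = 0.7. In power this is 60% against 82% at one end and 95% against 98% at the other.

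These sizes assume a linear scale, equal SDs at both times, d in endline SD units, 1:1 allocation and a design effect of 2.0 throughout. The value of r is unknown. The reading of 0.3 as a 35–71% relative reduction further assumes a yes/no outcome and a control prevalence between 10% and 40%.

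If only the meaning of d were at issue, this would be a reporting point. It goes further because baseline responses are already in hand and a more precise estimate is available without new data.

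**What to change.** Replace change as the primary outcome with a defined estimate: the difference between arms in endline past-year sexual violence, adjusted for each girl's baseline response and allowing for the planned clustering levels. A longitudinal mixed model that constrains the arms to a common baseline mean would serve equally well. State the scale of the outcome (yes/no, count or score), and make the change before endline data are seen.

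Alongside this, restate the detectable difference. If the outcome is yes/no, give it in percentage points at the prevalence observed in the completed baseline surveys, with the assumed r. Do this separately for Ethiopia and DRC, using for DRC only the girls aged 13–14 who were asked the violence questions.

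The cost is revised wording, a recalculation from data already collected, and a detectable effect that will look less favourable than d = 0.3 does now. No further recruitment or data collection is needed.

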## Methods

### Study design

Over three years (2014–2017), the COMPASS program is being implemented and evaluated in conflict-affected communities in the Democratic Republic of Congo (DRC), Sudanese refugee camps in Western Ethiopia, and in sites across Khyber Pakhtunkwa province in Pakistan, including Jalozai camp. In DRC and Ethiopia, the study design employs a wait-listed two-arm cluster randomized controlled trial. Given the exceedingly restrictive environment in Pakistan around issues of violence against girls, a mixed methods pre-post test is being implemented rather than an impact evaluation. Thus, the remainder of the study protocol manuscript will center on the trials taking place in DRC and Ethiopia. Further details of all study designs are found in Table 1. Qualitative inquiry will be used to complement the quantitative findings and to provide more nuanced understanding of processes of change and acceptability of programming.

**Table 1 Tab1:** Key study characteristics by COMPASS country site

Site	Primary research question	Study design	Quantitative surveys	Quantitative sample size at baseline
Conflict-affected communities in Kabare and Uvira territories, South Kivu Province, Democratic Republic of Congo	What is the incremental effectiveness of the parental curriculum, in addition to the core COMPASS programming, on improving girls’ safety and well-being?	Wait-list cluster randomized controlled trial + qualitative	10-12 year old CAPI survey^a^	886 girls (10–14 years)
			13-14 year old CAPI + ACASI survey	777 primary caregivers for girls
			Caregiver survey	
Refugee camps (Sherkole, Tongo, and Bambasi), Benishangul-Gumuz Region, Ethiopia	What is the overall effectiveness of the COMPASS program on improving girls’ safety and well-being, as compared to girls in the wait-list arm?	Wait-list cluster randomized controlled trial + qualitative	13-19 year old ACASI survey	919 girls (13–19 years)
Communities, and Jalozai camp in Khyber Paktunkwah Province, Pakistan	What is the overall acceptability and feasibility of COMPASS programming?	Pre-post test + qualitative	12-19 year old paper-based survey	208 girls (12–19 years)

^a^The 10–12 year old survey does not contain sensitive questions of sexual health

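### The DRC primary outcome is asked only of girls aged 13–14, but the 80% power and the 704-girl requirement count all girls aged 10–14

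*Protocol article*

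**What the plan says.** All references are to the protocol article.

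- **Randomization, sample size, and power analysis.** The calculation is for "80 % power to detect a Cohen’s effect size of d = 0.3 between treatment versus wait-list groups", with "α < 0.05 statistical significance level, a design effect of 2.0". It concludes that "a sample size of 704 girls is required in each country". For DRC it adds: "After accounting for an expected attrition rate of 25 % in DRC, the final sample size required at least 880 girls", and reports 886 surveyed. The same section says that "35 girl groups across 14 villages in South Kivu were divided into two age strata", 10–12 and 13–14 years, with 20–25 girls per group. It does not give the number of girls or groups in each stratum.
- **Study design, Table 1.** The 886 DRC girls are aged 10–14. The table footnote says of the instrument for ages 10–12 that the "survey does not contain sensitive questions of sexual health".
- **Quantitative assessment and analytic plan, with Table 3.** There is one girl primary outcome, past-year sexual violence. For DRC the section then states: "Only the older groups of girls (aged 13–14) were asked violence and sexual health modules given ethical concerns".

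The article gives no other power statement, no sample size for the older stratum and no different primary outcome for DRC.

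**The concern.** The number used to claim 80% power and the number of girls who can supply the primary outcome are not the same. The 10–12 stratum is counted in full towards 704 and 880, but it is never asked about sexual violence. The DRC primary analysis can use only the older girls and only the older groups among the 35. Physical and emotional violence, among the secondary outcomes, carry the same restriction.

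Two things are at stake. First, a reader will take the DRC trial as adequately powered for its primary outcome, so a non-significant result could be taken as evidence of no effect when the design could reliably detect only a considerably larger one. Second, the sample is described as girls aged 10–14, whereas the primary conclusion can apply only to ages 13–14.

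**Working it through.** **Inputs from the article:** d = 0.3; power 80%; α = 0.05; design effect (DE) 2.0; 25% attrition; 886 girls and 35 groups in DRC.

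**Assumptions:** two-sided test (this reproduces the stated figure); 1:1 allocation (ratio not stated); share *s* of the 886 aged 13–14 taken as 40%, 50% or 60% (not stated; 40% would follow if the five single-year ages were equally frequent); older groups taken as 35 × *s*.

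**Step 1: reproduce the plan's figure.** A two-sample t-test with d = 0.3, two-sided α = 0.05 and 80% power needs 175.4 girls per arm, rounded up to 176. Then 176 × 2 arms × 2.0 = 704. The stated figure is reproduced, and 880 = 704 × 1.25.

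**Step 2: restrict to girls aged 13–14.**

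- Analysed girls: N = 886 × *s* × 0.75
- Effective number per arm: n = N / (2 arms × DE 2.0) = N / 4
- Non-centrality: 0.3 × √(n/2)

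Example at *s* = 50%: N = 886 × 0.5 × 0.75 = 332; n = 332.25/4 = 83.1; non-centrality = 0.3 × √41.5 = 1.93, just below the critical value of about 1.97, so power is just under one half.

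| Share aged 13–14 | Enrolled | Analysed (25% loss) | Effective n per arm | Power at d = 0.3 | Power, df = older groups − 2 | Detectable d at 80% power |
|---|---|---|---|---|---|---|
| 40% | 354 | 266 | 66.5 | 40% | 36% (14 groups) | 0.49 |
| 50% | 443 | 332 | 83.1 | 49% | 44% (about 18 groups) | 0.44 |
| 60% | 532 | 399 | 99.7 | 56% | 52% (21 groups) | 0.40 |

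**Step 3: could any age split rescue the 80%?**

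- With 25% loss, even a 100% share gives 886 × 0.75 / 4 = 166.1 effective girls per arm and about 78% power. No split reaches 80%.
- With no loss at all, about 80% of the 886 would have to be aged 13–14.
- Keeping 80% power needs about 704 analysed girls aged 13–14. At 25% loss that is 704 / 0.75 = 939 enrolled, more than the whole DRC sample.

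**Step 4: sensitivity to the design effect.** With 25% loss, power for shares of 40%, 50% and 60% is:

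| Design effect | 40% | 50% | 60% |
|---|---|---|---|
| 2.0 | 40% | 49% | 56% |
| 1.5 | 51% | 60% | 68% |
| 1.0 | 68% | 78% | 85% |

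The younger and older groups share the same stated size of 20–25. Restricting by age removes clusters without shrinking them, so it gives no reason to assume a design effect below 2.0.

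**The case against.** **The sample size section does not name the outcome behind d = 0.3.** Cohen's d suits a continuous scale, and self-esteem, hope and gender norms look like scales, so the calculation may be generic. That is possible. But it is the only power statement, and the primary outcome is its natural reading. If it was meant for the all-age scales, then the DRC primary outcome has no stated power, and the article needs the same correction.

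**The restriction is disclosed and has an ethical reason.** This stands, and nothing here asks for it to change. The defect is that it was not carried into the sample size.

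**The percentages rest on assumptions.** This also stands. The age share, the group counts and 1:1 allocation are assumed, the design effect is the article's general one, and any gain from repeated measures in the mixed model is ignored. The figures are illustrative, but the direction is not in doubt, because a whole stratum supplies no primary-outcome data.

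**Part of the shortfall comes from the attrition step.** Multiplying 704 by 1.25 does not offset 25% loss; dividing by 0.75 would. The age restriction alone, applied to 704 analysed girls (n = 704 × *s* / 4), gives about 42%, 51% and 58% for the three shares, so this accounts for only about two percentage points.

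**The Discussion already cautions on interpretation.** It mentions short follow-up and contamination and plans to look at consistency across outcomes. It does not mention the missing younger stratum.

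**Conclusion.** The concern holds. The arithmetic behind 704 is correct, but it is applied to a population that is larger than the one asked the primary outcome. At the stated design effect and 25% loss, DRC power at d = 0.3 is about 40–56% if 40–60% of the girls are aged 13–14 (36–52% with degrees of freedom set by the number of older groups). The detectable effect is 0.40–0.49. The exact loss depends on an age split that the article does not give, but at the article's own design effect and attrition no split restores 80%. This concerns the primary outcome of one of the two trials and must be corrected. The Ethiopian trial is not affected, because its sample is aged 13–19.

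**What to change.** In the sample size section:

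1. Restate DRC power for past-year sexual violence from the actual number of girls aged 13–14 and the actual number of older groups. Both are known, because the article reports baseline as complete.
2. Give the effect detectable at 80% power with those numbers, allowing for attrition and clustering.
3. State that 704 and 886 apply in DRC only to outcomes asked of all girls, such as self-esteem, gender norms and hope.

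In the analytic plan:

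4. State that the DRC primary conclusion, and those for the other violence outcomes, are for ages 13–14.
5. State that a non-significant DRC result on these outcomes will not be read as evidence of no effect.

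The cost is rewording and a less favourable stated power for DRC. It needs no extra participants and no change to who is asked the violence questions.

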### Qualitative assessment and analytic plan

At baseline, methods of qualitative data collection included focus group discussions with caregivers and social mapping exercises with girls in both countries. In-depth interviews with girls and caregivers were also collected at baseline in DRC only. Similar activities will be conducted at endline. Focus group guides with caregivers sought to identify community gender norms related to girls and key challenges girls may face throughout periods of transitioning to adulthood in their communities, including challenges related to violence. Social mapping activities with girls involved asking girls to draw a map of their community and to note and discuss whether places were safe or unsafe. In-depth interviews with caregivers and girls sought to identify challenges girls face and how members of the family or community can support girls.

In DRC, qualitative data collectors were trained to conduct the group activities and record hand-written focus group or mapping notes in either Swahili or Mashi. In-depth interviews with girls and caregivers were audio recorded, transcribed, and then translated into English. In Ethiopia, Ethiopian qualitative data collectors facilitated the group activities in English with assistance from female Berta/Funj or Regarig translators. Only these two languages were selected for the qualitative research in Ethiopia due to challenges locating available female translators who could also speak either English or Amharic to communicate with the qualitative facilitators. All hand-written notes were recorded in English and subsequently transcribed. A combination of inductive content analysis and grounded theory will be utilized for data analysis to generate connections and themes across qualitative data.

